**Table 1 Tab1:**
[figure not shown]
SPIRIT schedule of enrolment, interventions, and assessments

##### Group 1 participants consent

Parental consent is required for participation of the 11–13-year-old students in the RiY trial. Letters will be sent home to parents as per usual school protocol*.* Many secondary schools have methods of secure electronic distribution of letters for student consent, parent/guardian information sheets and consent forms will be distributed through these electronic platforms if this is the preference and standard protocol of the school. The parent/guardian information sheet will explain the purpose of the study and the involvement required and provide an opportunity for parents to agree to participation. The letter will be sent ideally at least 1–2 weeks prior to the sessions to give ample opportunity for parents to provide consent. The consent form will encourage parents to discuss participation with the student to ensure the students and parents/guardians are agreeable and informed. Additionally, an informational video will be produced, reading the parent information sheet in *English and other languages such as Urdu, Arabic, Hindi and Polish*; this will be disseminated to schools to provide increased information and accessibility to parents with English as a second language. To ensure assent from the participants, the research team will deliver a short introductory assembly to ensure the participants are fully informed and happy with the information they have been provided about the programme. They will have the opportunity to ask any questions and refuse to take part without being disadvantaged in any way.

No consent is required to attend the RiY education sessions. Explicit positive consent is a requirement of participation in the programme for collection of oral health indices and questionnaire data. However, the intervention (classroom teaching sessions led by the RiY-peer leaders) will be delivered to the intervention classes; in most schools this will include other non-consenting students. These non-consented students will benefit from the educational component of the teaching but will be omitted from any data collection and analysis.

To facilitate evaluation of the programme and explore added benefits to the RiY-peer leaders, they will be invited to provide written optional consent to undergo dental assessments, saliva sampling (as part of the YUK-Oral Bugs citizen science project), complete oral health questionnaire and quiz. This will allow researchers to evaluate if RiY-peer leaders receive oral health benefits as a result of taking part in the programme. The participants will be fully informed with a detailed Participant Information Sheet and provided with the opportunity to refuse/withdraw without being disadvantaged in any way.

##### Process evaluation

Feedback will be gained from key stakeholders, NQD team and staff at schools predominantly at the end of the trial to explore their experiences/perspectives regarding operational considerations and the opportunity to suggest improvements/modifications to further enhance the RiY programme.

NQD, staff and RiY-peer leaders will be invited to participate in these feedback focus groups or individual semi-structured interview sessions at participants’ preference. NQD can participate as members of the RiY research team without participating in these feedback sessions. The feedback will facilitate the researchers in documenting and evaluating whether the RiY programme can be beneficial for the NQD, peer leaders, and schools and understanding how to improve the programme.

Consent for participation in feedback surveys and/or focus groups or individual interviews will be required from RiY-peer leaders, NQDs and members of staff of the collaborating schools. Participant information sheets will detail the purpose of the feedback sessions, the format of the feedback sessions, the opportunity to refuse participation, anonymisation and storage of collected data. Participant information sheets will be given 1–2 weeks prior to holding feedback sessions, and consent will be collected prior to data collection by the research team.

#### Randomisation

Only Group 1 participants (11–13-year-olds) will be randomised to receive intervention or control on a form level at a 2:1 or 3:1 ratio. As it is a feasibility trial, it will be a convenient proportion based pragmatically on the school’s form structure, timetabling, and availability of our team to oversee it in the individual participating schools.

The size of year group in each participating school will vary, but group allocation will allow for approximately two-thirds of the participants to receive the intervention and the remaining one-third as a control group.

An independent allocator will be given the recruitment numbers per class to perform the randomisation and then inform the schoolteachers of the randomisation allocation.

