**Methods:**

This is a UK school-based, assessor-blinded, parallel two-arm randomised controlled feasibility trial with a preliminary interim assessment in advance of progression to a larger scale trial in the future. The trial aims to recruit *n* = ~240 11–13-year-old participants and *n* = ~50 16–18-year-old peer leaders across five schools/colleges in West Yorkshire. The primary outcomes are related to feasibility in terms of recruitment and retention of participants, and the ability to deliver the intervention. The secondary outcomes include the oral health of participants (knowledge, attitudes and behaviour, plaque and gingival index) and process evaluation.

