### Trial design

The RiY feasibility trial is a UK school-based, assessor-blinded, two-arm randomised controlled trial (RCT). The feasibility trial will be conducted over two to three school academic years with an interim analysis planned at the end of Academic Year 1. The findings of the interim analysis will inform possible changes required to improve operational delivery in subsequent academic years. The study will be carried out in secondary schools in West Yorkshire serving a diverse population with high dental needs. Up to five participating schools will be targeted for this study.

This intervention will be a multicomponent complex intervention comprising two main parts: (1) a short classroom-based oral health education session including three interactive workshops; (2) a reinforcement session including three interactive workshops (YUK-Oral Bugs). Participants in the control group will receive the classroom-based oral health education session after the final follow-up assessments have been completed to avoid contamination of the data collection, but access will be ensured for all to the main RiY session, so that no one is disadvantaged.

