#### Study population and setting

A feasibility trial allows identification of key challenges with implementing a complex intervention and operational delivery in the school setting that is unfamiliar with undertaking RCTs. This trial aims to recruit up to five UK secondary schools with an integrated Sixth Form/Sixth Form Colleges and their feeder secondary schools. A formal sample size calculation was not used for this feasibility trial. Rather a pragmatic approach will be adopted informed by the systematic review of Parker et al. [37] looking at health interventions in schools, guidelines developed by Teresi et al. [38] for designing feasibility and pilot studies, and the BRIGHT trial that worked with similar aged adolescent participants delivering an oral health intervention in schools randomised by forms within year groups [5] using a target of *n* = 60 per year group/school. The focus in RiY is on practical considerations, needing to work within a tight budgetary constraint, but considering primarily the number of participants needed to reasonably evaluate feasibility goals of recruitment and retention of students alongside collecting process evaluation data on logistical components of working in school settings located with catchment to an underserved community with high oral health inequalities and often high ethnic diversity, alongside needing to assess the training of peer leaders that is a novel delivery approach of RiY’s oral health promotion. For 11–13-year-old participants, the target recruitment will be at least four classes per school with all students invited (class size is typically *n* = ~30 students/class) achieving *n* = ~240 participants (~*n* = 48 11–13-year-old participants/school); it is expected that this sample size will provide sufficient data to inform a future main trial. This trial will work closely with teachers to ensure that the intervention has minimal interruption to normal school curriculum and timetabling.

For 16–18-year-old peer leaders, the target recruitment will be *n* = ~50 peer leaders (10–12 participants per school/college).

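### The 2:1-or-3:1 form ratio does not agree with the two-thirds/one-third participant split, and a ratio set school by school gives the arms different school mixes

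*Protocol article*

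**What the plan says.** The Randomisation section of the protocol article says that Group 1 participants "will be randomised to receive intervention or control on a form level at a 2:1 or 3:1 ratio". It explains the open ratio on feasibility grounds: "it will be a convenient proportion based pragmatically on the" form structure and timetable of each school and on whether the team is available to oversee it there. The next paragraph accepts that year groups vary in size but says that "group allocation will allow for approximately two-thirds of the participants to receive the intervention and the remaining one-third as a control group". On the mechanism it says: "An independent allocator will be given the recruitment numbers per class to perform the randomisation".

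Under Study population and setting, "the target recruitment will be at least four classes per school with all students invited", with about 48 participants per school. The Trial design section sets the number of schools: "Up to five participating schools will be targeted for this study". The abstract gives the overall target: "The trial aims to recruit *n* = ~240 11–13-year-old participants". The article states that no formal sample size calculation was made.

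Table 2 bases progression mainly on recruitment and retention. Among its other considerations it lists evidence of benefit on toothbrushing at about 10–12 weeks, both within individuals and between the randomised groups.

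**The concern.** The Randomisation section describes the allocation twice, once as a ratio of forms and once as a share of participants. The two descriptions agree for one of the permitted ratios and not for the other. The ratio that disagrees is the only one open to a school at the planned minimum number of forms. A reader planning the main trial from this article would therefore expect more controls than such schools can supply.

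The second matter follows from letting the ratio vary between schools. A 3:1 school contributes relatively more to the intervention arm than a 2:1 school does. School is then associated with arm in the pooled data, even though forms are randomised within each school. Schools may well differ in baseline oral hygiene, so a comparison that ignores school would partly measure that difference.

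**Working it through.** **Inputs.** Ratios of 2:1 or 3:1 by form, and a split of about two-thirds/one-third of participants (Randomisation). At least four classes and about 48 participants per school (Study population and setting). Up to five schools (Trial design). About 240 participants (abstract). Assumptions: the classes and the forms are the same units, and forms within a school yield similar numbers of consenting pupils.

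**The plan's own figures.** 5 × 48 = 240, so the target reproduces. For a ratio r:1 the intervention share is r/(r + 1).

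- r = 2: 2/3 = 66.7%, so 160/80 of 240. This matches the stated split.
- r = 3: 3/4 = 75%, so 180/60 of 240. This does not match. Controls are (80 − 60)/80 = 25% fewer.

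**Which ratio is possible for a given number of forms.** Whole-form splits give:

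| Forms | Exact 2:1 | Exact 3:1 |
|---|---|---|
| 4 | none | 3 and 1 |
| 5 | none | none |
| 6 | 4 and 2 | none |
| 7 | none | none |
| 8 | none | 6 and 2 |
| 9 | 6 and 3 | none |
| 12 | 8 and 4 | 9 and 3 |

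A four-form school at 3:1 reaches two-thirds of participants only if the single control form supplies 48/3 = 16 consenting pupils and the other three supply (48 − 16)/3 = 10.7 each. With equal forms, each supplies 48/4 = 12.

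**Overall split when schools differ.** With k of five equal schools at 3:1 and the rest at 2:1, the intervention share is [k × 0.75 + (5 − k) × 2/3]/5:

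| k | Intervention share | Intervention/control of 240 |
|---|---|---|
| 0 | 66.7% | 160/80 |
| 1 | 68.3% | 164/76 |
| 2 | 70.0% | 168/72 |
| 3 | 71.7% | 172/68 |
| 4 | 73.3% | 176/64 |
| 5 | 75.0% | 180/60 |

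**School mix.** Take school A at 2:1 (32/16) and school B at 3:1 (36/12), 48 pupils each. School A supplies 32/(32 + 36) = 32/68 = 47.1% of the intervention arm and 16/(16 + 12) = 16/28 = 57.1% of control, a gap of 10.1 percentage points. With no intervention effect, the crude difference in means is (0.471 − 0.571) × (mean A − mean B), or about 0.10 times the school difference in size.

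With five schools of 48, the 2:1 schools' share of each arm is:

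- k = 1: 128/164 = 78.0% against 64/76 = 84.2%, a gap of 6.2 points
- k = 2: 96/168 = 57.1% against 48/72 = 66.7%, a gap of 9.5 points
- k = 3: 64/172 = 37.2% against 32/68 = 47.1%, a gap of 9.8 points
- k = 4: 32/176 = 18.2% against 16/64 = 25.0%, a gap of 6.8 points

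If all schools use the same ratio (k = 0 or 5), the gap is zero.

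**The case against.** The strongest reply is that the stated split is only approximate and counts participants, while the ratio counts forms, so the two need not match exactly. The class number is a minimum, and schools with six or nine forms can be exactly 2:1. All of this is true. It makes the mismatch a disagreement in one of two permitted options rather than a flat contradiction. It does not remove it, because a four-form school cannot be 2:1 and a quarter fewer controls is more than rounding.

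A second reply is that little depends on the split. The primary outcomes are overall recruitment and retention percentages, the quantitative analysis is descriptive, and no power is claimed. This stands, and it is why the point is minor.

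A third reply is that nothing in the article prescribes a crude pooled comparison, and that handling of school commonly belongs to the analysis plan, which is not shown. This also stands. The school-mix effect is a consequence of the chosen design that any comparison by randomised group in Table 2 has to respect; it is not an omission from the article.

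A reader might go further and infer that, because the allocator receives class recruitment numbers, those numbers decide which forms become controls. The document does not support this. Forms are said to be randomised, by an independent allocator. The word convenient describes the proportion, not the choice of forms. Class counts are compatible with a properly constrained randomisation, and recruiting before allocation limits recruitment bias. The article does not say how the counts are used.

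**Conclusion.** The concern holds in a limited form and is minor. The two-thirds/one-third split agrees with 2:1 but not with 3:1, and 3:1 is the only one of the two ratios available to a school at the planned minimum of four forms. The expected intervention share is about 67% to 75%, and at the upper end there are 60 controls rather than 80. These figures assume equal schools, forms of similar consented size, and schools allocated at exactly 2:1 or 3:1.

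Where ratios differ between schools, the arms differ in school mix by about 6 to 10 percentage points in the configurations worked above. A crude pooled comparison would be shifted by that fraction of the difference between school means; a comparison within school would not. The documents give no school means, so the shift cannot be put on an outcome scale.

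No loss of power and no biased choice of control forms can be concluded from the text.

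**What to change.** - Before allocation, record for each school how many forms go to each arm according to its form count, for example 3:1 for four or eight forms and 2:1 for six or nine. Where neither ratio is exact, as with five or seven forms, write down the split to be used.
- State that forms are drawn at random within school. If class recruitment numbers are used at all, limit this to a constrained randomisation specified in advance.
- Restate the expected split as about 67–75% intervention and 25–33% control.
- Make any comparison between arms within school, that is, stratified by school.

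The cost is a few sentences of protocol wording and a short table of form counts prepared earlier. The one downside is that the participant split will not be exactly two-thirds.

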#### Blinding

Prior to baseline data collection, participants will be assigned individual numerical participant IDs. The assessors (RiY Dentists and NQD, i.e. those undertaking data collection and dental checks) will be blinded to group allocation.

RiY-peer leaders will deliver the intervention to the class and hence cannot be blinded. Nonetheless, they will not participate in data collection. Statisticians and data analysts will also be blinded to allocation. Unblinding procedures are not required for an educational intervention.

#### Intervention

The RiY intervention meets the Medical Research Council definition of a complex intervention in terms of the interactions between components, recognition of the contextual factors and resources required to support reach and impact for implementation and the complexity of oral health behaviours studied [42]. RiY is embedded within the school’s delivery of the national curriculum on dental health and looking after teeth covering the benefits of good hygiene, healthy eating habits, and regular dentist check-ups [43]. The intervention group will receive two oral health education sessions each comprising three interactive, immersive workshops delivered by trained peer leaders assessed as being competent by the RiY research teams as oral health educators using consistent criteria. The *first session* delivers the main RiY intervention that expands on the national curriculum topics and the *second session* is the YUK-Oral Bug reinforcement on the science behind tooth decay introducing the oral microbiome and the importance of toothbrushing. The control group will receive only the standard school curriculum on dental health delivered by schoolteachers. After collection of RiY post intervention follow-up data, the control group will receive a delayed main RiY intervention session, delivered by RiY-peer leaders or teachers depending on timetable availability.

The Group 1 intervention group will attend classroom-based interactive, immersive workshops led by the RiY-peer leaders supported by the RiY Core Research Team or NQD. Each session will be the length of a normal lesson within the school (approximately 55–60 min). This will include three ‘hands-on’ workshops comprising:RiY Main InterventionSugar (healthy eating)Toothbrushing (oral hygiene)Going to the dentistYUK-Oral Bugs Reinforcement Session:Bugs card game: using flash cards that contain interesting facts about basic oral microbiota (Knowledge)Brushing the germs workshop: using plaque disclosing tablets to demonstrate efficient toothbrushing (toothbrushing skills)Making tooth brushing work for me (strategies for behaviour change)

##### Training of NQD

NQD will be pre-identified by the Associate Postgraduate Dental Dean for Yorkshire and the Humber via expression of interest emails. They will then specify their preference to be involved in teaching, fieldwork, or both. They will then receive the relevant online training for teaching or/and calibration in dental indices.

##### Training of RiY-peer leaders

Expression of Interest will be sought from eligible 16–18-year-old students; the schoolteachers will facilitate the final selection process to the target recruitment of approximately 10–12 students per participating school/college. Training to become a RiY-peer leader includes a 2-day conference at the University of Leeds and an additional YUK-Oral Bugs Reinforcement training session. The selected 16–18-year-old students from the secondary schools/college will attend the conference following written parental permission. The first day will involve didactic teaching introducing RiY, career pathways, *The Science of Tooth Decay* and *Child Oral Health*. The students will then be assigned to groups where each group will practise delivering the three workshops (*Toothbrushing*, *Sugar* and *Going to the Dentist*). They will be trained by NQD and supported by the RiY Research Team.

We will aim for an ~2–3-week interval between days 1 and 2 of the conference to provide sufficient time for RiY-peer leaders to consolidate learning from day 1.

The morning of the second conference day will start with an ice breaker followed by a morning workshop refresher and time to practise in small groups to gain feedback from the supporting NQD and RiY Research team. The afternoon will provide the 16–18-year-old students an opportunity to apply their learning in a real-life situation at the training school located a short coach ride from the University. The NQD and RiY Research Team will support, assess competencies and feed back to the students with the aim to accredit them as RiY-peer leaders competent as oral health educators by the end of the conference.

A further training session for the YUK Oral Bugs reinforcement session will be provided to RiY-peer leaders at their schools prior to delivery of this reinforcement session.

A full risk assessment for the conference day visits to the University of Leeds and training visit to the training school will be submitted to the School of Dentistry, University of Leeds, and shared on request with participating schools.

#### Outcome measures

The following feasibility outcomes have been included to help determine if progression to a full trial is operationally achievable, specifically:

#### Feasibility outcomes (refer to Fig. 1 feasibility study flowchart)

**Fig. 1 Fig1:**
[figure not shown]
Study flowchart

Recruitment rate of 11–13-year-old participants, withdrawal, and acceptability of randomisationFeasibility of training RiY-peer leaders as peer leader oral health educatorsFeasibility of deploying NQDAbility to collect dental health data & link to school's dataSaliva sample collection for YUK Oral Bugs citizen science projectI.Number of participants consenting to saliva samplingII.Ability to collect saliva samples in schools at baseline and post-intervention 

#### Clinical efficacy (secondary outcomes using validated clinical indices and questionnaires)

Change in toothbrushing skills via Plaque Index using the Turesky Modification of the Quigley-Hein Plaque Index (TQHPI) (calibration of the NQD will be described separately) and Gingival Index using bleeding on probing following the BRIGHT trial protocol for the same age students (baseline and post-intervention) [5, 44]Knowledge/attitude/behaviour via Adapted WHO Oral Health questionnaire (baseline & post-intervention)[45]DMFT/dmft score (recorded only at baseline)

#### Process evaluation

Questionnaires developed by the RiY research team based on the topic guides for the focus group/semi-structured interviews are available for use with key stakeholders (e.g. NQD, RiY-peer leaders and teachers) to understand RiY experience, school logistics Impact of RiY on school, year 7/year 8 students, logistics and feasibility of student participation.

